#### PREDICT sample size

For a prognostic model at least 20 EPV is needed to optimize reliability and to avoid bias in regression coefficients [37–39]. Based on having maximally 16 variables with a minimum of 20 events per variable, a prevalence of 30–40% after an initial sprain, including a 10% loss-to-follow-up, a sample size of 1185 patients is needed to perform the internal and 1185 patients is needed to perform the external model validation, resulting in a total of 2370 patients (Table 2).

During the study the required sample size may change and will be recalculated accordingly in case one of the following scenarios occur:In case one or more radiographic factors have a low inter- or intra-observer reliability (ICC ≤0.70), they will be excluded from the risk assessment model and the sample size will be recalculated using the new number of prognostic factors. If radiographic assessments cannot be performed in more than 2 cases (> 5%) a candidate predictor will be excluded, as the problem is likely to recur and therefore cannot be adequately assessed, now and during future assessment (e.g. up to 5% missing data is accepted) [40, 41].In case of multicollinearity between (ICC > 0.70) between prognostic variables one will be excluded;If a variable lacks agreement (ICC ≤0.70) with CAI it will be excluded;In case the prevalence of CAI during the study differs from the estimated 30%. In case the percentage of patients progressing to CAI exceeds the 50%, the sample size calculation will be based on the number of non-events. The prevalence will be recalculated when 500, 750, 1000, 1250, 1500, 1750,2000 and 2250 patients have returned the last questionnaire to minimize patient burden, as inclusion will stop as soon as the minimal required sample size is reached.

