### Data analysis and statistics

Demographics of the study population will be analyzed using the descriptive statistics. All statistics will be performed with SPSS version 23.0 (SPSS Inc., Chicago, IL, USA) and R package ‘Stats’ version 3.3.3 (University of Auckland, Auckland, New Zealand). A *p*-value of < 0.05 is considered significant. Normality of data will be assessed using the Shapiro-Wilks test.

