#### Prognostic value of variables

Depending on normality of data the Pearson or Spearman correlation coefficients will be used to assess correlations. A scatterplot for numerical data and Odds Ratio (OR) for binary data will be used to provide additional information on possible correlations in the data between prognostic factors. In case of correlations (*p* < 0.10 to avoid overfitting [40]) shown by an univariate analysis, a multivariate logistic regression will be performed to assess dependency between variables. The R^2^ will be used to visualize model fitness for the contribution of a factor to the progression to CAI and for the full model.

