#### Prognostic model

For internal validation a maximal amount of data is required to increase the reliability, therefore apparent validation will be used, including the full sample size of 1026 patients. To increase reliability the bootstrapping procedure will be used in the development of the model. A sample of 1000 bootstraps will be used to assess bias in the regression coefficients. Additionally the sensitivity, specificity and ROC curve will be used to assess the predictive value of the model.

To define generalizability of the created model, temporal validation is chosen to decide whether patients will be included in the internal or external validation database. After determining the prognostic value of the included variables, the full required sample size is calculated. Additionally the duration until this sample size will be reached, is estimated. Subsequently the time stamp for the temporal validation is decided. This ensures both sample sizes will be sufficient and reached. Again the sensitivity, specificity and ROC curve will be used to assess the suitability of the model [36].

Variables with a significant correlation with CAI (age, sex, height, BMI, sports intensity, varus/valgus alignment, fibular position, tibiotalar contact ratio, height medial malleolus and talar convexity), in addition to a continuous model, will be categorized to provide a binary model that can be easily implemented in daily practice by simply answering question by ‘yes’ or ‘no’. For this the Youden index and a ROC curve will be used [33]. For both models the final objective is to create a model with cut-off values that advises surgery, watchful waiting or no surgical treatment by combining the scores with the patients expectations in the shared decision making process.

The cut-off values will be reflected to the MDC, SEM and MCID to ensure minimal measurement bias.

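### Predictors are screened at p<0.10, the bootstrap only assesses coefficient bias, and calibration is not measured, so predicted CAI risks will on average be too extreme even at 20 events per variable

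*Protocol article*

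**What the plan says.** **Selection.** Data analysis and statistics, Prognostic value of variables: predictors go forward to a multivariable logistic model "In case of correlations (*p* < 0.10 to avoid overfitting [40]) shown by an univariate analysis".

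**Model and validation.** Data analysis and statistics, Prognostic model: internal validation is apparent validation on the full development sample. Bootstrapping is used in developing the model, with one specific purpose: "A sample of 1000 bootstraps will be used to assess bias in the regression coefficients". Performance in development, and again in the temporal sample, is judged by sensitivity, specificity and the ROC curve. R² is also planned, as a measure of fit. No calibration measure is named for either sample.

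**Cut-offs.** The same subsection uses the Youden index and a ROC curve to turn variables into yes/no items. Both the continuous and the binary model are then to have cut-offs giving three-way advice about surgery, weighed together with the patient's expectations.

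**Sample size.** Sample size calculation, PREDICT sample size: "For a prognostic model at least 20 EPV is needed to optimize reliability and to avoid bias in regression coefficients". The calculation is "Based on having maximally 16 variables with a minimum of 20 events per variable", with "a prevalence of 30–40% after an initial sprain, including a 10% loss-to-follow-up".

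**The concern.** A coefficient kept because it was significant in the data that also estimate it is, on average, too far from zero. More events per variable (EPV) make this smaller but do not remove it. The screen is described as a guard against overfitting, yet screening on significance in the development data is itself a source of overfitting.

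The consequence is a calibration slope below 1 in new patients: high predicted risks are too high and low ones too low. The named performance measures would not reveal it. Sensitivity, specificity and the ROC curve depend on how patients are ordered, and R² in the development data says nothing about agreement in new patients.

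The Discussion wants patients identified as at risk to be properly informed about treatment options, so the absolute risk attached to the high-risk group has a practical use.

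**Working it through.** **1. The plan's own sample size.** 20 × 16 = 320 events. At 30% CAI, 320 × 3.33 = 1065.6 patients, and 1065.6 / 0.9 = 1184 (1185.2 using 320 / 0.30). The stated 1185 reproduces, and 2 × 1185 = 2370. The Prognostic model subsection instead gives 1026 for the development sample: 1026 × 0.30 = 308 events, or 308 / 16 = 19.2 per variable. That discrepancy is a separate matter. The checks below use about 1066 analysed patients.

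**2. Expected shrinkage without simulation.** Heuristic factor S = 1 − 16/LR, with LR = −n ln(1 − R²_CS) and R²_CS = Nagelkerke R² × [1 − exp(2(0.3 ln 0.3 + 0.7 ln 0.7))] = Nagelkerke R² × 0.705. The protocol gives no R², so a range is assumed. Example at Nagelkerke R² = 0.10: R²_CS = 0.0705, LR = −1066 × ln(0.9295) = 78.0, S = 1 − 16/78.0 = 0.80.

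| Assumed Nagelkerke R² | 0.05 | 0.10 | 0.15 | 0.20 | 0.30 |
|---|---|---|---|---|---|
| S at 20 EPV | 0.58 | 0.80 | 0.87 | 0.90 | 0.94 |

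So 20 EPV does not by itself fix the amount of overfitting; predictor strength matters as much.

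**3. Simulation of the stated steps.** 30% CAI, 16 candidates, univariable p<0.10 screen, then an ordinary logistic fit in the same patients. Effect sizes and correlations are assumptions.

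Set A: n = 1066, six real predictors, 80 runs, tested in 30,000 new patients.

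| OR per SD | Slope | Top tenth: predicted / observed | Gap (points) |
|---|---|---|---|
| 1.2 | 0.78 | 48.8% / 43.7% | +5.1 |
| 1.3 | 0.90 | 55.8% / 52.6% | +3.2 |
| 1.5 | 0.95 | 67.3% / 66.3% | +1.0 |

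Set B: n = 1067, 200 runs, tested in 40,000 new patients, correlation between candidates 0 / 0.3.

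| Real predictors (log OR per SD) | Mean slope | Gap in top tenth (points) |
|---|---|---|
| six at 0.50 (strong) | 0.95 / 0.93 | 2.6 / 2.4 |
| four at 0.35 (moderate) | 0.92 / 0.89 | 3.1 / 3.3 |
| five at 0.15 (weak) | 0.68 / 0.80 | 4.8 / 4.9 |
| sixteen at 0.10 (very weak) | 0.62 / 0.89 | 6.2 / 3.9 |

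The 0.89 in the last row is not a weak-model result: sixteen correlated small effects add up, and observed risk in the top tenth is then 62.9%. The mean slope is below 1 in every row. Single datasets vary: the 5th to 95th percentile is 0.83 to 1.10 for strong uncorrelated predictors and 0.44 to 0.95 for five weak ones.

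**4. Would applying the planned bias assessment repair it?** In a re-run of Set A (uncorrected slopes 0.78 / 0.89 / 0.94), the already selected model was bootstrapped and the estimated coefficient bias subtracted. The slopes became 0.78 / 0.90 / 0.95, practically unchanged. The bootstrap slope with the predictors held fixed was 0.92 / 0.94 / 0.96, too favourable. With selection repeated in each resample it was 0.80 / 0.87 / 0.93, close to the truth.

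**5. Effect of the remedy in Set A.** Shrinking by the selection-repeating bootstrap slope gave slopes of 1.00 / 1.03 / 1.03 and top-tenth predictions of 45.0% / 52.6% / 65.0%, against observed 43.7% / 52.6% / 66.3%.

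**6. Effect on cut-offs.** Uniform shrinkage replaces a + b′x by a* + S·b′x with S > 0. The order of patients is unchanged, so the Youden maximum falls at the same patients. In Set B, classification with and without shrinkage agreed in 0.998 to 1.000 of patients.

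**The case against.** **Silence in an article.** What is done with a bootstrap bias estimate could be settled in the full plan, and the article does say that bootstrapping is used in model development. This stands in part: the text does not say that coefficients stay uncorrected. But the article states what the bootstraps are for and which measures judge the model, and step 4 shows that applying a coefficient-bias estimate from a fixed selected model would leave the slope where it was.

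**The EPV sentence.** A reader might infer that coefficients are left unshrunken because 20 EPV is thought to remove bias. The document does not make that link. It says that "at least 20 EPV is needed to optimize reliability and to avoid bias in regression coefficients", which is a necessary condition, and it plans a bootstrap check as well. The sentence needs a qualification, not deletion.

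**Cut-offs.** A reader might also infer that every cut-off would be misplaced. The only method the plan names, Youden with ROC, is rank-based, so step 6 rules this out. No absolute-risk threshold is fixed anywhere. What remains is conditional: three-way advice needs two thresholds, one Youden point supplies one, and a threshold set on the risk scale would be affected.

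**Size.** The protocol gives no effect sizes. With OR 1.5, the top-tenth error goes from +1.0 to −1.3 points after shrinkage, so nothing is gained there. This stands.

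**Temporal sample.** A separate sample of 1185 is planned, in which miscalibration could be measured and corrected. That is true, but the measures listed for it would not show the problem.

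**Conclusion.** The concern holds in a limited form. Selection at p<0.10, apparent validation, a bootstrap that only assesses coefficient bias, and no calibration measure in either sample together give predicted risks that are on average too extreme, with nothing listed that would detect it.

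The size depends on assumptions. The slope is about 0.6 to 0.8 with weak predictors and 0.93 to 0.95 with strong ones, and top-tenth risk is over-predicted by about 1 to 6 percentage points. Weak effects are plausible for some candidates: Clinical outcome measures says that three of the radiographic variables (MDTA, MMHA and TCA) have no previously shown correlation with ankle instability. A single dataset can still have a slope at or above 1.

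The simulations select and fit in the same patients. Assessment of agreement places the screen at 10 EPV; if the model is then refitted on the larger development sample, the overlap is only partial, and that case was not simulated.

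Risks told to patients and thresholds on the absolute-risk scale are affected. Which patients a Youden or ROC cut-off flags is not.

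**What to change.** In Data analysis and statistics, Prognostic model, replace the stated purpose of the bootstraps with wording such as:

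*The 1000 bootstrap samples repeat the full predictor selection. Their mean calibration slope is used to shrink the coefficients and the intercept is re-estimated (or an equivalent penalised fit is used). Calibration slope and intercept are reported in the temporal validation sample alongside the measures of discrimination.*

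In PREDICT sample size, add that 20 EPV limits overfitting but does not remove bias from data-driven selection.

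Cost: analysis wording only, since the 1000 bootstraps and the temporal sample are already planned and no further patients or data are needed. The downsides are slightly smaller odds ratios and little gain if the predictors prove strong.

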### Study centres and participants

This study will be conducted at the ER of four Dutch hospitals: the AMC Amsterdam, Flevoziekenhuis Almere, Slotervaart Medical Center Amsterdam, VUmc Amsterdam. All subsequent patients that present themselves at the ER of one of the participating hospitals after an initial lateral ankle sprain will be treated according to standard protocol, including anamnesis, physical examination and (in case of positive Ottawa Ankle Rules (OAR)*) a radiograph [24]. When a mortise view and lateral radiograph is made and negative for ankle fractures or other joint pathology, patients are screened for eligibility according to the in -and exclusion criteria (Table 1).

**Table 1 Tab1:** Inclusion- and exclusion criteria

Inclusion criteria	Exclusion criteria
At least 16 years old	Present fracture or other joint pathology/bone matrix pathology
Visited the ER within one week after a lateral ankle sprain	A diagnosed OCD after primary inclusion
Agreed with being approached for this study	Medial ankle instability
Reported anterolateral ankle pain after an ankle sprain or ankle distortion	Previous ankle surgery
Filled out the baseline, 3-, or 6 month questionnaire; and the 12 month follow-up	An unreliable radiograph due to the angle in which it is made or low quality
	Acute surgical repair or the ATFL/CFL or any other form of surgery within 12 months after the ER visit

*Abbreviations*: *ER* Emergency Department, *AP* anteroposterior, *OCD* osteochondral defect, *ATFL* anterior talofibular ligament, *CFL* calcaneofibular ligament

*The OAR are a requirement at the ER according to Dutch protocols to conclude whether there is an indication for a radiograph. However, in cases of severe LAS patients there is a high risk at false positive OAR despite the absence of a fracture (due to a painful lateral malleolus with or without the ability to bear weight).

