By including only patients that visit the ER and of whom a radiograph is made due to positive OAR, only the ‘severe’ ankle sprains are included. For these patients persisting complaints are most expected. Additionally, these patients remain in the picture by the treating physicians and can therefore receive proper follow-up. However, the strictness of following the OAR per ER is unknown and this creates a selection bias because not all sprains, of which a radiograph is made, score positive on the OAR. Also patients that were already experiencing chronic complaints may be included. For this reason an extra analysis will be performed to assess how many patients already experience recurrent sprains and whether the model is also fitting for these patients. However, it can be argued that, if the prognostic model fits the patients that develop CAI, it should also fit the patients that have already progressed to CAI. Another possible limitation of this study is the unknown adequacy of the specific set of selected radiographic factors that will be implemented in this model. By means of a literature search multiple radiographic characteristics that may be correlated to CAI were identified. However, most were validated using weight-bearing radiographs, which cannot be made after sustaining a severe ankle sprain. For this reason, the subtalar and talar tilt angle are excluded from this study as these are dependent on a weight-bearing condition.

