There is a rising demand for prognostic models that aid in risk analysis [43–46] and choice of treatment [44, 47–49]. Most models reflect the need of large study cohorts and multiple measurements over time [43, 47, 49]. However, sample size calculation and power analysis are often absent [44, 46, 49–51] or studies include a convenience sample based on the amount of retrospective data available [43, 45, 47]. This often leads to an imbalance between the number of studied predictive factors and the number of patients with the studied condition. Despite the claim of (internal and/or external) validity of the model, methods for validation are not described [49] or are absent [50]. To ensure we would not encounter these problems, our sample size and methods are developed following state-of-the-art directions [36]. Doing so, with a relatively heterogenic population, we anticipate to create a valid risk assessment model, based on easily identifiable factors and well suited for severe ankle sprain patients in clinical settings outside the current study settings. A valid risk assessment model may facilitate clinical decision making when a low or high risk at a certain disorder has been identified. This article may function as State-of-the-Art support for other researchers, interested in prognostic factors and in developing their own model to improve clinical practice.

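### The only planned test of generalisability is a temporal split within the same four hospitals, so nothing planned tests the expectation that the model will suit settings outside the study

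*Protocol article*

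**What the plan says.** - **Source of patients.** Study centres and participants names the only sites: "the AMC Amsterdam, Flevoziekenhuis Almere, Slotervaart Medical Center Amsterdam, VUmc Amsterdam". No other source is named anywhere.
- **Split.** Data analysis and statistics, Prognostic model, gives the purpose: "To define generalizability of the created model, temporal validation is chosen". The same sentence gives the role of the split: "temporal validation is chosen to decide whether patients will be included in the internal or external validation database". Performance in the second set is judged, as in the first, by sensitivity, specificity and the ROC curve.
- **Size and label.** PREDICT sample size: "a sample size of 1185 patients is needed to perform the internal and 1185 patients is needed to perform the external model validation". The Discussion presents the work as including both internal and external validation.
- **Expectation.** Later in the Discussion, the authors anticipate a model "well suited for severe ankle sprain patients in clinical settings outside the current study settings".
- **Possible hospital effects.** The Discussion concedes that "the strictness of following the OAR per ER is unknown and this creates a selection bias". Under Analyses, Inter- and intra-observer reliability, the observers come from one hospital. If the measurements prove reliable, they are rolled out to the other hospitals after a calibration meeting and practice session.

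**The concern.** A later cohort from the same emergency departments shows whether performance holds over time. It does not show whether the model carries over to a department with a different referral pattern, radiographic practice or group of readers.

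The article gives two reasons why the hospital could matter. Use of the Ottawa rules influences who gets a radiograph, and so who enters the cohort; how strictly each department applies them is not known. The radiographic predictors are proven in one hospital and then passed to three others.

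If baseline risk or measurement does differ by hospital, a temporal split with a similar hospital mix in both periods averages over the difference. The named performance measures, pooled over hospitals, respond little to it. A good result could then be read as evidence for other settings. That matters because the stated end product is a set of cut-offs that feed into advice on surgery or watchful waiting, where a shifted predicted risk has consequences.

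**Working it through.** **1. The plan's own figure.** Inputs from PREDICT sample size and Table 2: 16 coefficients, 20 events per variable, 30% risk, 10% loss.
- Events: 20 × 16 = 320.
- Patients: 320 × 3.33 = 1065.6; divided by 0.9 = 1184. With the exact 320 / 0.30 / 0.9 the result is 1185.2. Stated: 1185.
- Doubled: 2370, as stated.

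The size of the second set reproduces. The issue is where its patients come from, not how many there are. (The Prognostic model section gives 1026 for the internal sample. That is a separate inconsistency and does not affect this point.)

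**2. What each planned step can show.**

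| Step | Patients | New hospitals | Question answered |
|---|---|---|---|
| Apparent validation with bootstrap | Earlier, same four hospitals | 0 | Optimism, coefficient bias |
| Temporal validation | Later, same four hospitals | 0 | Stability over time |
| Expectation for outside settings | None planned | 0 | Not tested |

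**3. Would the pooled measures reveal hospital differences?** The article gives no between-hospital figures, so this is an illustration. Assumptions: four equal hospitals, the same predictor distribution in each, 30% overall risk, within-hospital AUC about 0.72, and the same hospital mix in both periods.
- Pooled AUC with no hospital difference: 0.724. With hospital risks spread from 23% to 37%: 0.719. I reran this simulation with evenly spaced risks, and the fall was no larger.
- Overall calibration under the temporal split: take risks of 23, 27.7, 32.3 and 37%. Their mean is 120 / 4 = 30% in both periods, so predicted and observed risk agree.
- Lowest-risk hospital held out: predicted (27.7 + 32.3 + 37) / 3 = 32.3%, observed 23%. On the log-odds scale: ln(0.23/0.77) − ln(0.323/0.677) = −1.21 + 0.74 = −0.47.
- Highest-risk hospital held out: predicted (23 + 27.7 + 32.3) / 3 = 27.7%, observed 37%. On the log-odds scale: −0.53 + 0.96 = +0.43.

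The planned measures barely move, whereas calibration by held-out hospital shows the shift.

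**4. Is leave-one-hospital-out feasible with 2370 patients?** Shares by hospital are not given, so a range is shown, after 10% loss.

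| Held-out share | Enrolled | Events held out at 30% (40%) | Development events at 30% | Development events per variable |
|---|---|---|---|---|
| 10% | 237 | 64 (85) | 576 | 36 |
| 25% | 593 | 160 (213) | 480 | 30 |
| 40% | 948 | 256 (341) | 384 | 24 |

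Development stays above the protocol's own 20 events per variable throughout.

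**5. Precision.** Treating the developed model as fixed, the standard error of the calibration intercept is at least 1/√(n·p·(1−p)).
- At a 25% share, n = 533: 1/√(533 × 0.21) = 0.095, so a 95% half-width of about 0.19.
- At a 10% share, n = 213: 1/√(213 × 0.21) = 0.15, so about 0.29.

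A shift of the size in step 3 would be visible at either size, but smaller ones would not be in a small hospital.

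**The case against.** Temporal validation is a recognised method, sometimes counted as a weak form of external validation, and the article says openly that it is what will be done. A reader might infer that the word external is itself an error. The documents do not support that: the fault lies in relying on the split for a question it cannot answer.

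The Discussion's statement on outside settings is worded as an anticipation and rests partly on a heterogeneous population. That stands: it is an expectation, not a claimed result. Still, no planned analysis tests it.

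Reporting by hospital could be set out in an analysis plan that is not shown. For that reason the point rests on the chosen test and the statements attached to it, not on missing detail.

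The remedy also stays within the same four hospitals. This is true, and it is why the wording must be narrowed as well.

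Other stronger readings do not hold:
- **A data-driven split date.** The article says "Subsequently the time stamp for the temporal validation is decided" after the prognostic factors have been assessed. But the date follows from a required patient count and estimated accrual, and no route to bias is apparent.
- **Selection known to vary by hospital.** The article says only that strictness in applying the Ottawa rules is unknown.
- **Both halves measured after one shared calibration session.** The text describes a session for the first observers and a later meeting for the other hospitals.
- **Miscalibration in every new department.** Nothing in the article shows this, since between-hospital differences are not given.

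**Conclusion.** The concern holds in a limited form. The one test assigned to generalisability is temporal, within four hospitals, and is judged by measures that respond little to differences in baseline risk between them. The expectation for settings outside the study is therefore untested: 1185 of 2370 patients go to this set, and it includes no new hospital. Those patients are not wasted, because stability over time is worth knowing.

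The conclusion rests on two assumptions. The first is that the later patients come from the same four hospitals, which is inferred because no other source is named. The second is that the hospital mix is broadly similar in both periods; accrual by hospital is not given. How much hospitals actually differ is unknown, so the figures in step 3 show what the planned check could miss, not what it will miss. This should be changed, but it does not invalidate the study.

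**What to change.** 1. In Data analysis and statistics, Prognostic model, keep the temporal split and describe it as temporal validation, a test of performance in later patients at the same hospitals.
2. Add leave-one-hospital-out (internal-external) validation: develop the model on three hospitals, test it on the fourth, and repeat for all four. Report calibration intercept, calibration slope and AUC with confidence intervals for each held-out hospital.
3. In the Discussion, limit both the external-validation statement and the expectation for other settings to later patients in these hospitals and to what the held-out-hospital results show. State that transport beyond the four hospitals remains untested.

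Cost: one further analysis of data already collected, plus wording; no extra patients. The downside is wide intervals for smaller hospitals and a less favourable label than external validation.

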#### Inter- and intra-observer reliability

The inter- and intra-observer reliability will be analyzed using the Intraclass Correlation Coefficient (ICC) Two-Way Mixed model on absolute agreement in case of normally distributed data. Reliability is considered poor if the ICC is ≤0.40, moderate between 0.40 and 0.70, good between 0.70 and 0.90, and excellent > 0.90 [41]. In case of skewed data the Cronbach’s alpha will be calculated. In case of an ICC of > 0.70 a Bland and Altman plot will be drawn to visualize the measurements and their relation to the limits of agreement.

Additionally the Standard Error of Measurement (SEM: SD x √(1-ICC)) and Minimum Detectable Change (MDC_95%_: 1.96 x √2 x SEM) \ will be calculated to objectify the ICC.

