### Adverse events

No study-related adverse events are expected as the study contains an observational cohort with 1 set of radiographs made according to standard protocol.

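### Of the three yardsticks named for the yes/no cut-offs, only SEM suits a radiograph read once, and no check of agreement at those cut-offs is stated

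*Protocol article*

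**What the plan says.** All places are in the protocol article.

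- **Binary model** (Data analysis and statistics, Prognostic model). Variables that correlate significantly with the outcome, radiographic ones included, "will be categorized to provide a binary model that can be easily implemented in daily practice". On how the cut-offs are found: "For this the Youden index and a ROC curve will be used". The section closes with the safeguard: "The cut-off values will be reflected to the MDC, SEM and MCID to ensure minimal measurement bias".
- **Reliability statistics** (Data analysis and statistics, Inter- and intra-observer reliability). The statistic is the "Intraclass Correlation Coefficient (ICC) Two-Way Mixed model on absolute agreement in case of normally distributed data", with Cronbach's alpha for skewed data and a Bland-Altman plot when the ICC exceeds 0.70. SEM is SD x √(1-ICC) and MDC is 1.96 x √2 x SEM.
- **Exclusion rule** (PREDICT sample size). "In case one or more radiographic factors have a low inter- or intra-observer reliability (ICC ≤0.70), they will be excluded from the risk assessment model".
- **Number of films per patient** (Adverse events). The study has "1 set of radiographs made according to standard protocol".
- **MCID.** It is not defined, valued or spelled out anywhere, including the abbreviation list. That list also gives SEM the expansion that belongs to SDC, in conflict with the formula above.

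**The concern.** The yes/no version is the one intended for everyday use, and the cut-offs are meant to feed into advice on treatment. A radiographic item in it is one reading of one film set against a fixed limit. What matters is how often a second reading would give the other answer.

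The safeguard does not address that directly. The MDC describes a difference between two readings. The MCID describes a change that matters to a patient, and a bone angle measured once shows no change. The reliability gate is an ICC on the measured value. An acceptable ICC does not guarantee a stable answer at a cut-off, particularly when many patients lie close to it. Radiographic items could therefore enter the binary model with answers that depend noticeably on who read the film.

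**Working it through.** **1. The plan's own reliability figure.** The reliability sample assumes 80% agreement and 20% relative error. The formula 1/(r² x pa²) gives 1/(0.20² x 0.80²) = 39.06, which matches the stated 39. The article gives no flip rate, observed ICC or derived cut-off, so what follows is conditional.

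**2. Width of the error band.** With the article's formulas at ICC 0.70, in SD units:
- SEM = √(1 - 0.70) = 0.548
- one reading against a fixed cut-off: 1.96 x 0.548 = 1.07
- MDC: 1.96 x √2 x 0.548 = 1.52
- ratio = √2 = 1.41, so the MDC band is 41% wider

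If the cut-off is at the median of a normal measure, 71.7% of patients lie within ±1.96 x SEM of it at ICC 0.70, 61.9% at 0.80 and 46.5% at 0.90.

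**3. How often the yes/no answer changes.** Assume two readings are bivariate normal with correlation equal to the ICC. For a cut-off at quantile p, with c = Φ⁻¹(p), P(discordant) = 2[p - Φ₂(c, c; ICC)]. At the median this is arccos(ICC)/π.

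| ICC | median | 40th pct | 30th pct | 20th pct | 10th pct |
|---|---|---|---|---|---|
| 0.70 | 25.3% | 24.5% | 21.9% | 17.4% | 10.6% |
| 0.80 | 20.5% | 19.8% | 17.8% | 14.2% | 8.8% |
| 0.90 | 14.4% | 13.9% | 12.5% | 10.0% | 6.2% |

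Kappa = (po - pe)/(1 - pe), with pe = p² + (1 - p)². At a median cut it is 0.49, 0.59 and 0.71 for the three ICCs. At ICC 0.70 it falls to 0.41 with a cut at the 10th percentile, although raw agreement is higher there.

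**4. The preset MDTA classes.** The limits of 87° and 91° are in the article. The mean of 89° and SD of 2° to 4° are assumptions. At ICC 0.70 the three-way class changes between readings in 29.7% (SD 2°), 39.0% (SD 3°) and 41.3% (SD 4°) of patients. With SD 3°, SEM = 3 x 0.548 = 1.64°, 1.96 x SEM = 3.22° and MDC = 4.55°. That MDC exceeds the whole 4° normal band.

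**5. Precision of the gate.** The 0.70 limit is applied to an estimate from 39 films. By a Fisher-z approximation for two readings, SE = 1/√37.5 = 0.163, and an estimate of 0.70 has a 95% CI of about 0.50 to 0.83. An item with true ICC 0.60 (29.5% discordant at a median cut) would pass in about 14% of cases.

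**The case against.** Several counter-arguments have force, and they rule out stronger readings that a reader might infer.

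- **That the safeguard is wrong altogether.** It is not. The sentence also names the SEM, which does fit one reading against a cut-off.
- **That SEM and MDC capture random error only, so they cannot bear on bias.** The documents do not support this. For normally distributed measures the ICC is on absolute agreement, so systematic differences between observers lower it and raise the SEM. A Bland-Altman plot is also planned for every item with ICC above 0.70.
- **That reliability is tested only on continuous values.** This is too absolute. The varus/normal/valgus class is one of the eleven radiographic variables that the abstract submits to reliability assessment, and the 39 films are sized on percent agreement. What remains is narrower: only ICC and Cronbach's alpha are named, and neither suits a three-class item.
- **That items passing the gate generally flip in one of four re-readings.** That figure needs an ICC at the limit, a cut-off at the median and bivariate normality. Youden cut-offs need not lie at the median.
- **That the damage would go unseen.** Sensitivity and specificity are estimated on cohort readings that already contain reading error, and again in temporal validation. A noisy item's poorer performance should show there. No decision rule uses the MDC, and a wider band errs on the cautious side.

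Two further objections stand in part. The preceding sentence uses the term cut-off values for the three-way treatment advice, so the link to the yes/no items is likely but not explicit. Under that reading too, the MDC and MCID of a radiographic measure do not suit a threshold on a model score. Agreement statistics for derived classes might also be left to a fuller document. This article, however, already fixes a specific safeguard, and the point is that two of its three parts do not suit radiographic cut-offs.

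**Conclusion.** The point holds in limited form. For radiographic cut-offs, the MDC is √2 too wide for a single reading, the MCID is undefined and inapplicable, and only the SEM is suitable. No stated check looks at agreement on the yes/no answer at the derived cut-offs. An item just above the ICC limit could change its answer in up to about 25% of re-readings. The range at ICC 0.70 is 10.6% to 25.3% by cut position, with maxima of 20.5% at ICC 0.80 and 14.4% at ICC 0.90.

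These rates assume bivariate normality and a true ICC equal to the stated value. The MDTA figures also rest on an assumed mean and SD. The point concerns only the radiographic items of the binary model. Age, sex, height, BMI and sports intensity are not read from films, and the continuous model is not dichotomised. It is a worthwhile and cheap improvement, not a threat to the study as a whole.

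**What to change.** In Data analysis and statistics, Prognostic model, rewrite the closing sentence on cut-offs:

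1. State which cut-off values are meant: those of the yes/no items, those of the treatment advice, or both.
2. For radiographic cut-offs, remove MDC and MCID as criteria and report the share of cohort patients within ±1.96 x inter-observer SEM of each cut-off.
3. From the 39 films already read twice by each observer, report inter- and intra-observer percent agreement and kappa, with 95% CIs, for the classes that each cut-off creates. Include the 87°/91° MDTA classes.
4. Use these results to decide whether an item is dichotomised or kept only in the continuous model.

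Item 4 should not become a rigid exclusion on the point estimate. With 39 films, a kappa of 0.49 (agreement 0.747, chance agreement 0.50) has SE √(0.747 x 0.253/39)/0.50 ≈ 0.14, so its 95% CI is about ±0.27.

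The cost is a little extra analysis on readings already planned, kappas that will be imprecise, and possibly fewer radiographic items in the binary model.
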